### Setting and patient recruitment

The study will take place at the Pain Center and the Department of Neurosurgery of Strasbourg University Hospital, in collaboration with researchers from the Institute of Cellular and Integrative Neuroscience (INCI) at the University of Strasbourg. Coordination and monitoring of the study will be carried out by the investigating team.

Patients will be recruited by the consulting neurosurgeon in the Department of Neurosurgery at Strasbourg University Hospital. Patients consulting for leg pain due to a disc herniation, for whom surgical intervention is indicated, will be referred for participation in this clinical study. During this routine consultation, a screening interview will be conducted for each potential participant using a questionnaire verifying eligibility criteria.

After verification of eligibility criteria, written information about the study will be provided to the patients, who will then be able to reflect on their decision to participate or not for approximately one week. Patients will be re-contacted by the study investigator, and, if they consent to participate, will attend an enrolment visit. After a final verification of eligibility, the patient will provide written informed consent.

In the consent form, participants will be asked if they agree to the use of their data, should they choose to withdraw from the trial. Participants will also be asked for permission for the research team to share relevant data with the Universities taking part in the research, or with regulatory authorities, where applicable. This trial does not involve collecting biological specimens for storage.

To improve adherence to intervention protocols, the neurosurgeon during the selection visit and the investigating physician during the inclusion visit will explain to the patient the expected benefits, in particular the reduction of neurogenic inflammation of the nerve root, the improvement of nerve healing and thus the potential prevention of chronic postoperative pain. To improve monitoring adherence, such as blood draws, they are taken with the patient's consent as part of the standard of care process. There are no additional visits related to the protocol.

The inclusion criteria are:Patient > 18 years old;Patient with a diagnosis of radiculopathy on lumbar disc herniation and for whom surgery has been scheduled in the Department of Neurosurgery;Patient affiliated to a social security health insurance scheme;Patient able to understand the objectives and risks of research and to give informed, dated and signed consent;Negative blood pregnancy test for female participants of reproductive age recorded at the inclusion visit and effective contraception used throughout the study.

The exclusion criteria are:Patient with a history of lumbar spinal surgery (multiple herniated discs, herniated disc other than lumbar);Patient with HIV, active cancer, HBV, HCV;Patient receiving long-term systemic corticosteroid therapy;Patient with an American Society of Anesthesiology (ASA) score > 3 during the routine pre-surgery consultation with the anesthetist;Inability to give the patient informed information (patient in an emergency or life-threatening situation, difficulties in understanding);Patient in exclusion period (determined by a previous or ongoing study);Subject under safeguard of justice;Subject under curatorship;Patient actively breastfeeding.

### Timeline and description of processes

An initial selection of patients will be carried out during a routine consultation with the practicing neurosurgeon, 30 days (± 20 days) prior to surgery. During this visit, the patient will be provided with the necessary study information, the eligibility criteria will be verified, and a clinical examination will be carried out. If the patient is eligible and decides to participate, an enrolment visit will be carried out 1 week (± 6 days) prior to surgery. At this visit, which takes place at the pain center (Strasbourg University Hospital), written informed consent is provided obtained from the participant, who will then complete baseline questionnaires and undergo a clinical examination. Randomization is also carried out at this visit, by using web-based randomization software (CleanWEB® clinical trial management platform). The details of randomization will remain unavailable to the medical examinator and the participant during the study. Randomization will be carried out using an allocation ratio of 1:1, which will determine the treatment arm of the patient: the interventional group (surgery and PRF application) or the control group (surgery alone). The allocation sequence is generated by the statistician of the study, using computer-generated random numbers. There will be no special criteria for discontinuing or modifying allocated interventions. To reduce predictability of a random sequence, the randomization will be carried out with two randomly distributed block sizes. Randomization will be carried out without factors of stratification. A specified investigator will carry out the enrolment visits and randomization process. This investigator and the surgeons carrying out the intervention will be the only investigators not blind to participants’ treatment arm. Blinding of the evaluating investigators will remain in place until statistical analysis of the study results has been finalized. Equally, participants are blinded to the intervention that they have received (experimental or control).

The day of surgery is designated as V0. At V0, a blood sample will also be collected for RNA extraction and genes of interest expression analysis, just before the surgery. This will be considered as the basal condition. The participant will be examined at two further visits: 2 weeks (± 5 days) post-surgery (V1) and 6 months (± 15 days) post-surgery (V2). These visits will consist of a clinical examination, a blood sample collection for gene expression analysis, and completion of questionnaires. Figure 1 shows a schematic chart of the study timeline.

**Fig. 1 Fig1:**
[figure not shown]
Schematic schedule of the NeuroPRF study. Asterisk symbol (*) indicates the following: variables carried out specifically for research purposes, outside of routine care; currency sign (¤) indicates the following: β-hCG test is carried out at a routine anesthetist consultation; D, days; M, months; AE, adverse event; SAE, serious adverse event; VAS, visual analog scale; DN4, Douleur Neuropathique 4; NPSI, Neuropathic Pain Symptom Inventory; SF-12, 12-item Short Form Survey; HAD, Hospital Anxiety and Depression

### Description of clinical examination and questionnaires

The baseline clinical examination carried out at the enrolment visit includes questions about pain descriptors and history. Medical history, comorbidities, and medications will also be documented. The clinical examinations carried out at V1 and V2 consist of a physical neurological examination including myotomal strength, reflex, and sensory testing (soft touch, pinprick, allodynia or hyperalgesia detection).

Participants will be asked to complete the following questionnaires:DN4 [24];NPSI [25];HAD [26];SF-12 [27];VAS for current leg pain [28];PGIC scale [29].

All are self-questionnaires, except for DN4, which will be carried out by the examining clinician. All questionnaires will be completed pre-operatively, at 2 weeks, and at 6 months post-operatively, with the exception of the PGIC scale, which will be completed only after the surgery (i.e., 2 weeks and 6 months post-operatively). Data from these examinations will be entered into the CleanWEB® e-CRF by the examining investigator.

### Description of interventions

Surgery will be carried out under general anesthesia for both groups. Surgical treatment of lumbar disc herniation relies on relieving the compression of the nerve root by the herniated disc. Prior to surgical incision, a blood sample of 5 mL will be taken for gene expression analysis. This must be carried out prior to surgery in order to avoid any systemic inflammatory phenomena caused by surgery itself.

*- Control group (surgery alone)*: The patient is placed in the knee-pectoral decubitus position under general anesthesia. The concerned intervertebral space is identified by radioscopy. The most common procedure implies a median posterior cutaneous incision, with subsequent detachment of the paravertebral muscles from the underlying vertebra. The interlaminar space is then approached through removal of the ligamentum flavum. Once the vertebral canal is accessed, epidural fat is retracted in order to visualize the dural sac and emerging spinal roots. Gentle traction on the dural sac and spinal roots allows exposure of the bulging disc at the compression point. The posterior longitudinal ligament is then incised and herniated disc removed with additional discectomy if necessary. Closure is finally performed with respect to each anatomical layer.

*- Interventional group (surgery and periradicular administration of PRF)*: The same surgical steps are carried out as those in the control group, with an additional periradicular administration of autologous PRF. Preparation of the PRF will be carried out during the surgery, in the operating theater. Twenty milliliters of venous blood will be collected from the perfusion device, in 2 sterile tubes without anticoagulant (Becton Dickinson‚ Vacutainer‚ 10 mL each), and immediately centrifuged at room temperature for 14 min at 1300 rpm in a suitable centrifuge (PRF duo, Process for PRF, Nice, France), according to the A-PRF protocol described by the manufacturer. Under the effect of coagulation activation and centrifugal forces, three layers will appear in the tube: a pellet of red blood cells at the bottom, an acellular plasma supernatant on the surface, and a PRF fibrin clot loaded with platelets in the middle. PRF in gel form is then recovered under sterile conditions by the neurosurgeon, who will shape it using tweezers so that it can be applied to the root lesion before layer-by-layer closing.

During the immediate postoperative period, all analgesics are permitted as per standard of care: paracetamol, NSAIDs, nefopam, tramadol, lidocaine, ketamine, morphine. For residual postoperative pain, level 1, 2, or 3 analgesics are permitted.

### Gene expression analysis

To study the mechanisms of initiation and maintenance of neuropathic pain, and in particular the involvement of the cytokinergic system [18], we will measure the expression of messenger RNA (mRNA) of selected pro-inflammatory and anti-inflammatory cytokines and signal transduction proteins (Table 1), extracted from peripheral blood mononuclear cells (PBMC). Indeed, the synthesis and release of cytokines are essentially ensured by glial and immune cells in neuropathic conditions [12]. These mononuclear immune cells therefore appear to be a good marker of cytokine involvement in the pathophysiological mechanisms behind the onset and maintenance of neuropathic pain [15].

A 5 mL sample of blood will be taken from participants at V0, V1, and V2 in a pseudonymized EDTA-anticoagulation LeucoSep vials (Greiner, ref.227288). Briefly, samples will be subjected to density gradient centrifugation (1000 × g, 10 min, 4 °C) to isolate PBMC. Collected PBMC will be washed (1000 × g, 10 min, 4 °C) in Hank’s buffer (Fisher Scientific, ref.24020–091), and red blood cells will be lyzed (Qiagen, ref.79217). After another wash (1000 × g, 10 min, 4 °C), two identical aliquots of highly-purified PBMCs will be collected; the first one will be resuspended in 600 μL of RNAlater Stabilization Solution (Invitrogen, ref.AM7020) and stored at – 20 °C for back-up. The second will be resuspended in 200 μL of 1-thiogycerol solution (Promega, ref.AS1340), vortexed and stored at – 20 °C for RNA extraction. Total RNA extraction will be performed on a Maxwell RSC device (Promega, ref.4500) according to the manufacturer’s instructions. Quality control will be performed on microfluidic chips prepared using the 6000 Nano Kit (Agilent) and loaded on the 2100 Bioanalyzer system (Agilent) according to the manufacturer’s instructions. RNA samples will be quantified on a Nanodrop 2000 spectrophotometer (Thermo Scientific). These high-quality, DNA-free RNA samples will then be stored at – 80 °C.

Four hundred nanograms of each RNA sample will be reverse-transcribed with the iScript gDNA Clear cDNA Synthesis Kit (Bio-Rad), which integrates an effective DNase digestion step to remove any trace contamination of genomic DNA.

Quantitative PCR will be performed using SYBR Green Supermix (Bio-Rad), on the iQ5 Real Time PCR System (Bio-Rad). Amplifications will be carried out in 42 cycles (20 s at 95 °C, 20 s at 60 °C, and 20 s at 72 °C). Primer sets for all genes of interest and housekeeping genes have been designed using Oligo6.0 and M-fold software. To ensure a high primer specificity and an optimal amplification efficacy for all primer sets in the given PCR conditions, we will use control samples to verify that amplification efficacy given by standard curves will be close to 100% (± 2%) and that amplification specificity, assessed by a melting curve study, will generate a single peak at the melting temperature expected by sequence analysis. Samples will be accurately dispensed in 96-well plates using a robotic workstation, for a final volume of 15 μL per well (Freedom EVO100; Tecan, Lyon, France). Targets will be amplified in triplicate, and threshold cycle (Ct) values will be determined. Fold changes in gene expression among groups will be calculated using the delta-delta Ct method. Gene expression data will be normalized to the arithmetic mean of housekeeping gene expression (ACTB, B2M, GAPDH and HPRT).

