### Statistical analysis

The analyses will be carried out using Bayesian methods.

Firstly, a descriptive analysis will be carried out. For the categorical variables, the frequency of each value and the cumulative frequency will be given. For the quantitative variables, location parameters (mean, median, minimum, maximum, first and third quartiles) and dispersion parameters (standard deviation, variance, range and interquartile range) will be given. The parameters will be estimated firstly on raw data, and secondly within the Bayesian paradigm, on the posterior distribution, for each variable.

Secondly, to compare the difference of the means of the VAS, a Bayesian linear regression will be performed. The regression will be simple linear or generalized depending on the distribution of the data. To meet the secondary objectives, Bayesian linear regressions will be performed for continuous variables, and Bayesian logistic regressions for categorical variables.

The regressions will be firstly carried out without adjustment and secondly with an adjustment on sex and age. Subgroup analyses are not planned.

The priors will be on the one hand very uninformative and on the other hand informative in the context of a sensitivity analysis.

For each analysis, the posterior distribution of the parameter of interest (rate, proportion, mean, odds ratio, regression coefficient, etc.) will be estimated using Markov chain Monte Carlo (MCMC) draws. The default number of iteration is 200,000 with a burning of 10,000 and a thinning of 2. Algorithm convergence will be assessed graphically and with the Gelman and Rubin’s convergence diagnostic. Autocorrelation will be assessed graphically and, if required, the number of iterations and thinning will be increased to reduce as much as possible the autocorrelation.

Credibility intervals will be calculated at 95% using the quantile method. A particular factor will be considered to exert an effect on the variable in question if the probability that the effect is greater than the reference value is greater than 0.975 or less than 0.025.

The proportion of missing data will be given for each variable. Missing data will be treated by simple deletion of cases if these values are very few or by multiple imputation in the opposite case.

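### Gene expression: read literally, the text leads to linear regression on a skewed fold-change ratio without baseline expression as covariate; log2 delta Ct adjusted for V0 would be more precise at almost no cost

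*Protocol article*

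**What the plan says.** All references are to the protocol article.

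- **Gene expression analysis.** The raw measurement is the threshold cycle: "Targets will be amplified in triplicate, and threshold cycle (Ct) values will be determined". Amplification efficiency is to be within 2% of 100%, and expression is normalised to the mean of four housekeeping genes. The derived quantity is then given: "Fold changes in gene expression among groups will be calculated using the delta-delta Ct method".
- **Timeline and description of processes.** Of the blood sample taken just before surgery (V0) it says: "This will be considered as the basal condition". Further samples follow at 2 weeks (V1) and 6 months (V2).
- **Aim and objectives; Outcomes.** The correlation of neuropathic pain with cytokine gene expression is a secondary objective. The level of expression of the genes in Table 1 (16 in all) is a secondary outcome.
- **Statistical analysis.** "To meet the secondary objectives, Bayesian linear regressions will be performed for continuous variables, and Bayesian logistic regressions for categorical variables". Regressions are run first unadjusted, then adjusted for sex and age. Just before this stands the sentence "The regression will be simple linear or generalized depending on the distribution of the data", which follows on from the VAS comparison and is not repeated for secondary variables. An effect is declared when its posterior probability is above 0.975 or below 0.025.

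**The concern.** At about 100% efficiency one cycle is about one log2 unit, so the Ct difference is already on a scale where doubling (+1) and halving (-1) are symmetric. Turned into a ratio, doubling lies 1 above the reference of 1 and halving only 0.5 below it. The ratio is right-skewed, and a few high values carry most of the information in a linear slope. That suits a panel poorly when it is meant to contrast pro- and anti-inflammatory genes.

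If the ratio is taken against V0, a second loss arises. All the V0 noise enters the outcome, whereas a covariate would remove only as much as the V0-V2 correlation supports. The planned adjustment (sex and age) does not include baseline expression.

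At stake is the precision of a mechanistic secondary objective in at most 60 patients.

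**Working it through.** **The plan's own figure.** No power or SD is given for gene expression. The only power stated is 93.5% for the VAS (25 per group, difference 1, SD 1). It reproduces: noncentrality 1 × √(25/2) = 3.54 on 48 degrees of freedom gives 93.4% with a two-sided t-test. It has no bearing on the gene analyses.

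**Assumptions.** Log2 expression is normal with SD s of 0.5, 1, 1.5 or 2 cycles (not in the documents). The true relation is linear on log2. The 0.975/0.025 rule is treated as a two-sided 5% test, as under a vague prior.

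**1. Expression as predictor of a continuous pain score.** With t = s × ln 2, the efficiency of the ratio relative to log2 is t² / (exp(t²) − 1).

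| s | t² | exp(t²) − 1 | Efficiency |
|---|---|---|---|
| 0.5 | 0.120 | 0.128 | 94% |
| 1 | 0.480 | 0.617 | 78% |
| 1.5 | 1.081 | 1.948 | 56% |
| 2 | 1.922 | 5.833 | 33% |

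Simulated power (20,000 runs):

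| Case | log2 | Ratio, s = 0.5 | s = 1 | s = 1.5 | s = 2 |
|---|---|---|---|---|---|
| 60 patients, log2 correlation 0.36 | 82% | 80% | 73% | 65% | 54% |
| 50 patients, log2 correlation 0.385 | 80% | 78% | 71% | 62-63% | 54% |

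**2. Influence.** Among 50 patients, the three most extreme carry on average 38%, 52%, 65% and 74% of the predictor's sum of squares on the ratio scale (s = 0.5 to 2), against 30% on log2.

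**3. Arm contrast, scale alone.** With 25 per arm, no baseline, and a log2 shift giving 80% power on log2, the ratio gives 78%, 71%, 60% and 47%. With no true difference, the ratio's rejection rate is 5.1%, 4.4%, 3.8% and 3.2%, near or below nominal.

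**4. Arm contrast, scale and baseline separated.** With 25 per arm, s = 1 and V0-V2 correlation r from 0.3 to 0.7 (8,000 runs):

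| Analysis | Power |
|---|---|
| log2 at V2, V0 as covariate | 71-73% |
| log2 change from V0 | 54-65% |
| Fold change from V0 | 42-60% |

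The step from the first row to the second has nothing to do with the ratio. The residual variance is s²(1 − r²) with the covariate and 2s²(1 − r) for the change, so the relative efficiency is (1 + r)/2: 65% at r = 0.3 and 85% at r = 0.7. Only the step from the second row to the third is due to the scale.

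**The case against.** The strongest objection is that the article never says a per-patient ratio is the variable in the regression. The fold-change sentence stands in a laboratory section and speaks of fold changes among groups, which may be a reporting summary. Delta-delta Ct is itself a difference in log2 units, so modelling Ct and reporting fold changes fits the text. Calling V0 the basal condition does not make it the denominator of a ratio. The modelling scale could also be set in a full protocol or SAP that is not shown. All this stands: a reader might infer that the plan has fixed the ratio as the analysis variable, and the text does not support that. What remains is narrower. The article does name a derived quantity, a model class and an adjustment set, and taken at their word these give an inefficient analysis.

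Three further limits also stand.

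- **Size.** It depends on an assumed SD. At 0.5 the loss is about 2 points of power. Linearity on log2, which favours log2, is assumed too.
- **Attribution.** A reader might put the whole arm-contrast drop down to the ratio. At SD 1 about half or more of it comes from not adjusting for V0.
- **False positives.** A reader might infer that outliers would create spurious findings. The simulated type I error does not show this; the harm is lost power and uneven influence.

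Finally, the Abstract speaks of correlating expression with the appearance of neuropathic pain. As a yes/no outcome that would go to logistic regression, which the figures above do not model.

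**Conclusion.** The point holds as a nearly free improvement to a secondary analysis, not as a fixed error. Followed literally, the text leads to linear regression on a right-skewed ratio without baseline expression as covariate.

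As a predictor, the ratio costs about 2 points of power at a log2 SD of 0.5, rising to 28 points at an SD of 2 (82% against 54%, 60 patients). For arm contrasts at SD 1, fold change from V0 gives 42-60% where log2 with V0 as covariate gives 71-73%, and the loss is shared between scale and missing baseline. These sizes rest on assumed SDs, log-normal ratios and a relation linear on log2; the fold-change-from-V0 figures further assume V0 as the reference.

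Type I error is not inflated, and the primary VAS analysis is untouched.

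**What to change.** Add a sentence to each of two sections of the protocol article's text (or the full protocol).

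- **Gene expression analysis:** the analysis variable is the housekeeping-normalised delta Ct (log2 scale) at the visit concerned. Fold changes are for reporting only.
- **Statistical analysis:** all gene-expression regressions use that variable. Where the question is a post-surgery arm contrast or a change since surgery, the patient's V0 delta Ct is a covariate. Coefficients and their 95% credible limits are back-transformed to fold changes for presentation.

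The cost is two sentences, settled before analysis. The V0 samples are already planned, so no new data, assays or patients are needed, and readers still see fold changes.

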### Safety considerations

Adverse events are defined as any undesirable experience occurring to a subject during the study. All adverse events reported directly by the subject or observed by an investigator will be recorded. In the case of a suspected unexpected serious adverse reaction (SUSAR), the pharmacovigilance officer, in collaboration with the sponsor and investigators, will carry out the unblinding of the participant in question, via the CleanWEB® interface. There is no criterion or formal stopping rules. Indeed, the treatment is unique and, intraoperatively, there is no criterion for definitive discontinuation of the use of the experimental product as such. There is a very small risk that the treatment cannot be administered during surgery for logistical, medical or other reasons. Thus, the patient would then be withdrawn from the study.

No data monitoring committee was envisioned because the study was a low-risk intervention. However, the investigators agree to comply with the requirements of the sponsor and the competent authority for an audit or inspection of the study (Additional file 1). Consistency checks of the collected data will be performed by computer according to predefined rules between the sponsor and the investigator described in the monitoring plan. Requests for information or “queries” will be sent to the investigator to correct or clarify specific data. Any modification of data will be traced back via an audit trail that can be consulted with the CLEANWEB® software. A clinical research associate, delegated by the sponsor, will visit the study center at the beginning of the trial, then during the trial at the rate of once a year during the trial and at the end of the trial.

